**Modifications to clinical study protocol (version 2.0)**

The main modifications in version 2.0 compared with version 1.1 are as below:

1. As the reporting time of partial laboratory examinations, such as serological examination, is long and unable to be completed within the specified timeframe in the original protocol (version 1.1), the screening/wash-out period is prolonged to Day -14.
2. Course of therapy in the protocol summary: modified from “a total of 7 weeks, including wash-out period of one week and treatment period of 6 weeks” to “a total of 8 weeks, including wash-out period of 2 weeks and treatment period of 6 weeks”.
3. 4.1 Study method: modified from “this study is comprised of two periods: screening and wash-out period (1 week), double-treatment period (6 weeks). Screening eligible subjects with major depressive disorder will enter the one-week placebo wash-out period and receive placebo two tablets, once per day, for consecutive 7 days.” to “this study is comprised of two periods: screening and wash-out period (2 week), double-treatment period (6 weeks). The 1st period is one screening and wash-out period of 8 days (recommended) to up to 14 days, screening eligible subjects with major depressive disorder will enter the one-week placebo wash-out period and receive placebo two tablets, once per day, for consecutive 7 days. ”.
4. Visit 1 in the study flow chart: time modified from “-8~-1d” to “-14~-1d”.
5. Addition of footnote 1 in the flow chart: “screening/wash-out period: Day -14~-1, all the subjects will be given the drugs for wash-out period on Day -8 and enter one 7-day wash-out period (-7 ± 1d)”.
6. Follow-up procedure: 7.1 Screening/wash-out period modified from “Visit 1—— Day -8~-1” to “Visit 1—— Day -14~-1”.
7. The description of secondary efficacy variable “change in visual analogue scale- pain intensity (VAS-PI)” is specified and modified to “change in visual analogue scale- pain intensity (VAS-PI), including overall pain, headache, back pain, extremity or joint pain, abdominal pain and other pain”.
8. The time of AE record in “9. Adverse event reporting” is clarified and mofidied from “in this study, record of adverse event is mainly the subjective symptoms and physicochemical examination after administration” to “in this study, adverse event (serious adverse event and non-serious adverse event) from the signature of informed consent form to the last visit will be recorded”.
9. A small number of editorial changes.

[14. Summary Report 42](#_Toc1640)

[15. Amendment to study protocol 42](#_Toc14750)

[16. Publication 42](#_Toc13400)

[17. Archival of materials 43](#_Toc3721)

[18. References 43](#_Toc19081)

[Attachments 44](#_Toc31165)

[Appendix 1: Hamilton Depression Scale -17 (HAM-D_17_) 44](#_Toc14775)

[Appendix 2: Clinical global impression scale (CGI) 47](#_Toc27517)

[Appendix 3: Hamilton Anxiety Scale (HAMA) 48](#_Toc12734)

[Appendix 4: Visual Analog Scale – Pain intensity (VAS-PI) 49](#_Toc31283)

[Appendix 5: Description of amendment clinical trial protocol 51](#_Toc1372)

List of Abbreviations

| **English Abbreviation** | **Definition** |
| --- | --- |
| 5-HT | 5-hydroxytryptamine |
| AE | Adverse event |
| ALT | Alanine aminotransferase |
| ANCOVA | ANCOVA analysis |
| AST | Glutamic-oxaloacetic transferase |
| AUC | Area under the concentration-time curve |
| BP | Blood pressure |
| CFDA | National Medical Products Administration |
| CGI-I | Clinical global impression scale-Overall improvement |
| CGI-S | Clinical Global Impression scale-Severity |
| C_max_ or Cmax | Maximum plasma concentration |
| Cr | Creatinine |
| CRF | Case Report Form |
| CYP 450 | cytochrome P450 enzyme |
| DA | Dopamine |
| DAT | Dopamine transporter |
| DBP | DBP |
| DSM-IV-TR | Diagnostic and Statistical Manual of Mental Disorders, 4th edition, revised |
| ECG | Electrocardiogram |
| ECT | Electroconvulsive therapy |
| FAS | Full analysis set subset |
| FT3 | Tri-iodothyronine free |
| FT4 | Thyroxine free |
| GCP | Good Clinical Practice |
| h | Hour |
| HAMA | Hamilton Anxiety Scale |
| HAM-D_17_ | Hamilton Depression Scale - 17 |
| LOCF | Last observation carried forward |
| MAOIs | Monoamine oxidase inhibitor |
| MDD | Depressive disorder |
| NaSSA | Noradrenergic and specific 5-serotonergic antidepressant |
| NDRIs | Norepinephrine and dopamine reuptake inhibitor |
| NE | Norepinephrine |
| NET | Norepinephrine transporter |
| NOAEL | No observed-adverse-effect level |
| ODV | *O*-desmethylvenlafaxine |
| PI | PI |
| PPS | Per Protocol Population |
| SAE | Serious Adverse Event |
| SBP | SBP |
| SERT | 5-hydroxytryptamine transporter |
| SNRIs | 5-hydroxytryptamine and norepinephrine reuptake inhibitor |
| SSRIs | Selective Serotonin Reuptake Inhibitor |
| t_1/2_ | Half-life |
| TCAs | Tricyclic antidepressant |
| T_max_ | Time to maximum observed plasma concentration |
| TSH | Thyroid stimulating hormone |

Abstract

| **Sponsor** | Shandong Luye Pharma Co Ltd |
| --- | --- |
| **Investigational product** | Ansofaxine Hydrochloride Sustained-release Tablets |
| **Trial title:** | A Multicenter, Randomized, Double-Blind, Placebo-controlled, Dose-finding Clinical Trial to Preliminarily Evaluate the Efficacy and Safety of Ansufaxine Extended-release Tablets for the Treatment of Major Depressive Disorder (MDD) |
| **Objectives** | Primary objective:  To find the optimal dose of Ansufaxine extended-release tablets in the treatment of MDD.  Secondary objective:  To evaluate the preliminary efficacy and safety of Ansufaxine extended-release tablets for the treatment of MDD, thereby providing a basis for the determination of study design and dosing regimen for a phase 2I clinical trial. |
| **Subject Population** | Patients aged 18~65 years who meet DSM-IV-TR diagnostic criteria for major depressive disorder |
| **Number of subjects** | 5 groups, 52 subjects/group, a total of 260 subjects |
| **Study Methods** | Multicenter, randomized, double-blind, placebo parallel controlled, dose exploratory |
| **Investigational product** | 1. Study drug: Ansofaxine Hydrochloride Extended Release Tablet, specification 40mg, researched, developed and provided by Shandong Luye Pharmaceutical Co., Ltd. 2. Control drug: Simulator for Ansofaxine Hydrochloride Extended-release Tablet (placebo), researched, developed and provided by Shandong Luye Pharmaceutical Co., Ltd. |
| **Group and**  **Dosage and administration** | 1. Trial Grouping:   260 patients with major depressive disorder who meet the enrollment criteria will be randomized to 4 study drug dose groups of and 1 placebo group, i.e., 52 patients each group.   1. Dosage and administration:   Wash-out period: placebo two tablets, once per day, administered under fasted state or after meal at a relatively fixed time in the morning, for consecutive one week.  Treatment period: Ansofaxine Hydrochloride Extended Release Tablet 40mg, 80mg, 120mg, 160mg or placebo orally, once per day, administered under fasted state or after meal at a relatively fixed time in the morning, for consecutive 6 weeks. |
| **Course of therapy** | A total of 8 weeks, including a screening/wash-out period of two weeks and treatment period of 6 weeks. |
| **Visit frequency** | Follow-up at screening, baseline (Day 0), 1, 2, 4 and 6 weeks after administration. |
| **Inclusion criteria** | 1. Male and female outpatients or inpatients aged 18~65 years; 2. Subjects who meet the Diagnostic and Statistical Manual of Mental Disorders, Fourth Edition (DSM-IV-TR) criteria for MDD with a single or recurrent episode(296.2/296.3), without psychotic features; 3. Subjects who have 17-item Hamilton Depression Scale (HAM-D_17_) total score≥20 points at the screening and baseline visit; 4. Subjects who have Depressed Mood of Hamilton Depression Scale (HAM-D_17_) ≥2 points at the screening and baseline visit; 5. Subjects who have clinical Global Impression-Severity Scale (CGI-S) score ≥4 points at the screening and baseline visit; 6. Women of childbearing age (e.g., women who have not experienced sterilization or have had menopause for less than 1 year) who have negative result shown by the urine pregnancy test at the screening and baseline visit; male and female subjects of childbearing age who agree to use a medically acceptable form of contraception for the duration of the study and until at least 28 days after the last oral dose of the study medication; 7. Subjects who voluntarily participate in the trial and sign informed consent forms and who are able to comply with the procedures for scheduled visits, treatments, laboratory tests and other research procedures. |
| **Exclusion criteria** | 1. Subjects who are allergic or known to be allergic to venlafaxine and desvenlafaxine 2. Subjects who have previously failed treatment with venlafaxine at an adequate dose for an adequate time, or patients who have refractory depression and have previously failed treatment with at least 2 types of antidepressants at an adequate dose for an adequate time; 3. Subjects who have greater than 25% change in HAM-D17 total score at baseline from screening visit; 4. Subjects who have clear suicide attempt or behavior with Suicide score in HAM-D17 ≥ 3 points; 5. Pregnant or breastfeeding women, or men and women of childbearing age who do not use a medically acceptable form of contraception or fail to continue contraception until 28 days after the last dose of the study medication; 6. Subjects with DSM-IV-TR axis I diagnoses other than MDD, who receive treatment for such diagnoses (including current or previous diagnoses of anorexia nervosa or bulimia nervosa), or who have been diagnosed with depressive neurosis within the past 2 years;Depressive episode secondary to other psychiatric disorder or somatic disease; 7. Subjects with MDD secondary to other organic or mental disorders; 8. Subjects with a history of seizures (except spasms caused by infantile hyperpyretic convulsions); 9. Subjects who have received electroconvulsive therapy (ECT) within 3 months prior to screening or need current ECT treatment per investigator’s judgment, have received systematic psychotherapy (interpersonal relationship therapy, dynamic therapy, cognitive behavioral therapy) within 3 months of screening, have received transcranial magnetic stimulation (TMS) 3 months prior to screening, or have received light therapy 2 weeks prior to screening; 10. Subjects who have regularly taken anti-depressants within 2 weeks prior to screening, or have withdrawn from psychotropic drugs for less than 7 half-lives (at least 2 weeks for monoamine oxidase inhibitors and at least 1 month for fluoxetine) before randomization/enrollment; 11. Subjects with a history of serious unstable cardiovascular, hepatic, renal, blood or endocrine diseases; 12. Subjects with hypertension whose blood pressure is poorly controlled (SBP≥140 mmHg or DBP≥90 mmHg at the screening and baseline visit); 13. Subjects with a history of gastrointestinal diseases known to interfere with drug absorption or excretion, or those with a history of surgery that is known to interfere with drug absorption or excretion; 14. Subjects with a history of increased intraocular pressure or narrow angle glaucoma; 15. Subjects with clinically significant abnormal results as considered by the investigator shown by a physical examination, laboratory test or urine drug test (e.g., ALT or AST> 1.5 times the upper limit of normal; Creatinine clearance > the upper limit of normal; abnormal measurements of thyroid function which are of clinical significance); 16. Subjects with Electrocardiogram (ECG) abnormalities that are clinically significant at screening and baseline, and investigators believe that it is inappropriate for the subjects to be enrolled, such as QTc interval >450 ms for male and QTc interval >460 ms for female; 17. Subjects who have participated in clinical trials on other drugs within 3 months prior to screening; 18. Subjects with serious acute or chronic diseases, mental illnesses or clinically significant abnormalities as shown in laboratory tests, of which investigators believe that the subjects are not suitable for this study |
| **Efficacy evaluation**  **Variables** | Primary efficacy variable:  Changes from baseline in the total score of 17 items of Hamilton Depression Scale (HAM-D_17_) at the end of treatment  Secondary efficacy variables:   - Change in the Clinical Global Impression Scale-Improvement (CGI-I) score at the end of treatment - Change from baseline in the Clinical Global Impression Scale-Severity (CGI-S) score at the end of treatment - Change from baseline in the Hamilton Anxiety Scale (HAMA) at the end of treatment - Change from baseline in the Visual Analog Scale of Pain Intensity (VAS-PI) score at the end of treatment - Change from baseline in HAM-D_17_ factor scores at the end of treatment - HAM-D_17_ response rate (≥ 50% reduction from baseline in HAM-D17 total score) - HAM-D_17_ remission rate ( HAM-D17 total score ≤7) |
| **Safety Evaluation Variables** | - Adverse events - Vital signs, physical examination, laboratory tests (hematology, urinalysis, blood chemistry test and serological test), 12-lead ECG findings |
| **Statistical analyses** | To evaluate the LY03005 extended-release tablets effect compared to placebo on change from baseline in the HAM-D17 total score at end of week 6 by using analysis of covariance (ANCOVA) model, statistical tests were conducted using two-sided test and the difference was considered statistically significant (unless otherwise specified) when P value was ≤ 0.10. Adjustment was not made when using multiple tests. Intergroup differences on change from baseline in the HAM-D17 total score were compared using ANCOVA, including the HAM-D17 total score at baseline as a covariate, and adjusted by site effect. Difference of LSMEANs compared to placebo group and associated 90% Tukey-Kramer-adjusted confidence intervals will be tabulated.  The type and frequency of adverse events and relationship with the investigational drug would be summarized. Subjects discontinued the study due to AEs and those with severe or serious AEs were noted.  The shift tables will be used for the laboratory tests, ECG findings, physical examination (clinical significance will be based on the investigator’s judgment). Abnormal findings of clinical significance were listed.  Changes in the vital signs from baseline at each visit were described and descriptive statistics were calculated, which include the number of subjects, mean, standard deviation, median, minimum and maximum. Paired t-test was used to analysis the difference between post-treatment and baseline in the same treatment group. The differences of change from baseline between treatments groups were analyzed by using ANCOVA or rank sum test. |

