# Trial design

## Test method

This study was a multicenter, randomized, double-blind, placebo parallel-controlled, dose-finding phase 2 clinical trial to find the optimal dose of LY03005 extended-release tablets for the treatment of MDD and to evaluate the preliminary efficacy and safety, providing a basis for the design of phase 2I clinical trials and the determination of dosing regimens.

This study consisted of two periods: a screening and washout period of up to 2 weeks (8 days recommended) and a double-blind treatment period of 6 weeks. The screening and washout period were expected to last from 8 days (recommended) to 2 weeks. After screening, eligible patients with MDD entered a 1-week placebo washout period, during which they took 2 placebo tablets orally once a day in the morning for 7 consecutive days. 260 patients with MDD who still met the inclusion criteria after the placebo washout then entered a double-blind treatment period of 6 weeks. They were randomly assigned to placebo or one of four fixed does LY03005 extended-release tablets (40, 80, 120 or160mg/day) using a 1:1:1:1:1 randomization schedule. Subjects took 4 tablets of test drug or placebo once a day and returned for follow-up visits at the weekends of study week 1, 2, 4 and 6.

Efficacy endpoints included 17-item Hamilton Depression Scale (HAM-D17), Hamilton Anxiety Rating Scale (HAM-A), Clinical Global Impression (CGI) and Visual Analog Scale for Pain Intensity (VAS-PI). Safety evaluation included adverse events, vital signs, physical examination, laboratory tests (hematology, urinalysis, blood chemistry test and serological test), and 12-lead ECG.

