### Analysis of Efficacy

The final treatment evaluation will be the primary evaluation for all the primary and secondary efficacy variables. The double-blind treatment starts from the first dose of study drug, until the last dose of study drug. PPS and FAS are used for the analysis of efficacy. The analysis of PPS is based on the observed data. Unless otherwise specified, LOCF (last observation carried forward) and the observed data will be used for analysis of FAS.

The missing items of observations on the efficacy scale will be processed as described below: if up to 20% of the items are missing on one scale, the total score can be derived by multiplying the average of the available items by the total number of items. If more than 20% of the items are missing, the total score on this scale will be considered as missing. The missing total scores will be imputed using the LOCF method. For observed case (OC) analysis, the missing total scores will not be imputed. The baseline score will not be used to carry forward.

In the statistical model using study site as one independent variable the site with small number of subjects may be pooled. The anlaysis will be performed after the sites were pooled. The rules of pooled site will be provided in the statistical analysis plan, if necessary. In addition, this study is one exploratory analysis, and no adjustment of multiple tests will be carried out.

1. Analysis of the primary endpoints

The primary endpoint is the change in the total score of HAM-D_17_ scale from baseline at the final treatment evaluation, and the statistics including the number of subjects, mean, standard deviation, median, minimum and maximum will be calculated.

This is one dose-effect exploratory study, α for type I error is set as 0.1.

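### Dose-placebo differences are tested unadjusted at 0.10 but tabulated with 90% Tukey-Kramer intervals, so test and interval disagree when the unadjusted p lies between about 0.014 and 0.10

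*Protocol*

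**What the plan says.** In the protocol's Abstract, the row on statistical analyses compares each dose with placebo on change in HAM-D17 total score at week 6 by ANCOVA. On sidedness it says "statistical tests were conducted using two-sided test", and on the threshold "the difference was considered statistically significant (unless otherwise specified) when P value was ≤ 0.10". On multiplicity it says "Adjustment was not made when using multiple tests".

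Two sentences later, for the same model, it says: "Difference of LSMEANs compared to placebo group and associated 90% Tukey-Kramer-adjusted confidence intervals will be tabulated".

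The Analysis of Efficacy part of section 11.2 keeps the threshold ("α for type I error is set as 0.1") and the policy ("this study is one exploratory analysis, and no adjustment of multiple tests will be carried out"). It describes the same ANCOVA, with baseline score as covariate and treatment group and site as fixed effects. It never mentions Tukey-Kramer. No section says that the interval has a different purpose from the test, or which of them decides how a dose is read.

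The design is "5 groups, 52 subjects/group, a total of 260 subjects", allocated "using a 1:1:1:1:1 randomization schedule".

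**The concern.** A two-sided test at level 0.10 and a 90% confidence interval from the same model are normally two views of one result: the interval excludes zero when the test is significant. Here the interval carries an adjustment that the test does not, so the two can give different answers for the same dose.

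The text also conflicts with itself. The Abstract rules out adjustment and then prescribes one for the same four contrasts, while the detailed section lists only the unadjusted rule. What is at stake is how the primary efficacy table is read in a trial meant to find a dose. One reader applies the P ≤ 0.10 rule, another looks at whether the interval crosses zero, and both follow the protocol.

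The SAP is not at hand, but this is not a gap that a SAP could fill. The protocol itself fixes both rules.

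**Working it through.** **Inputs from the protocol.** Two-sided level 0.10; 90% interval level; 5 arms, hence 4 placebo contrasts and 5 × 4 / 2 = 10 pairs; 52 per arm; ANCOVA with treatment, site and one covariate. The number of sites, the SD and the expected effect are not given and are assumed below where needed.

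**Residual degrees of freedom.** With n per arm and s sites, df = 5n − 5 − 1 − (s − 1). For n = 52 and an assumed s = 10: 260 − 5 − 1 − 9 = 245. Smaller n allows for losses: 40 per arm matches the protocol's 200 valid cases, and 36 its 30% drop-out.

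**The protocol's own pairing first.** An ordinary 90% t interval has half-width t(0.95; df) × SE and excludes zero exactly when p is below 0.10. It reproduces the stated test.

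**The Tukey-Kramer interval.** Its multiplier is q(0.90; 5, df) / √2, where q is the studentized range quantile. The unadjusted p at which it just touches zero is 2 × P(T > multiplier).

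| n per arm | df | t multiplier | Tukey-Kramer multiplier | Ratio | Unadjusted p at boundary |
|---|---|---|---|---|---|
| 52 | 245 | 1.6511 | 2.4738 | 1.498 | 0.0140 |
| 40 | 185 | 1.6531 | 2.4785 | 1.499 | 0.0141 |
| 36 | 165 | 1.6541 | 2.4808 | 1.500 | 0.0141 |

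With 1 or 15 sites at n = 52 (df 254 or 240) the multipliers are 2.4733 and 2.4741, so the unknown number of sites does not matter.

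The adjusted interval thus excludes zero only when the unadjusted p is at most about 0.014. Per comparison it covers 1 − 0.014 = 98.6%. At df 245, an unadjusted p of 0.05 corresponds to a Tukey-Kramer p of about 0.284, and 0.10 to about 0.466.

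**Width.** At n = 52, SE = SD × √(2/52) = 0.196 SD. Half-widths are 1.6511 × 0.196 = 0.324 SD and 2.4738 × 0.196 = 0.485 SD. For an assumed residual SD of 6 to 8 points, that is 1.9 to 2.6 against 2.9 to 3.9 HAM-D17 points.

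**How often the two disagree, per comparison** (assumed true standardised effects, noncentral t, n = 52):

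| Effect | p ≤ 0.10 | Tukey-Kramer excludes 0 | Discordant |
|---|---|---|---|
| 0 | 0.100 | 0.014 | 0.086 |
| 0.2 | 0.269 | 0.075 | 0.194 |
| 0.3 | 0.453 | 0.175 | 0.279 |
| 0.4 | 0.652 | 0.334 | 0.318 |
| 0.5 | 0.815 | 0.531 | 0.284 |
| 0.6 | 0.920 | 0.721 | 0.200 |

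With no effect at any dose, the chance of at least one discordant dose among four is about 0.27 (simulation with a shared placebo arm, 1,000,000 runs).

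**Familywise error over the four placebo contrasts**, same simulation: about 0.286 unadjusted (1 − 0.9⁴ = 0.344 if they were independent) and about 0.048 with the Tukey-Kramer multiplier. A two-sided 10% Dunnett multiplier is about 2.17, which corresponds to an unadjusted p of about 0.031.

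**The case against.** The strongest reply is that the trial is exploratory, that simultaneous intervals beside unadjusted p-values merely add caution, and that the adjustment appears in one Abstract sentence which section 11.2 does not repeat. Much of this stands, and it limits the point. Four stronger readings are tempting, and the protocol does not support them.

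- **That p-values and intervals will contradict each other throughout.** They disagree only when the unadjusted p lies between about 0.014 and 0.10, and only one way: significant test, interval containing zero. Just above 0.014 the interval barely crosses zero.
- **That Tukey-Kramer is wrong for comparisons with placebo.** It is valid for them, only conservative (familywise error about 0.048 against a nominal 0.10). An all-pairs family also has some basis, since section 11.2 speaks of comparing treatment groups and exploring differences among doses. Preferring Dunnett is a matter of efficiency.
- **That the 90% label is false.** The label names the adjustment, so it discloses a simultaneous level. Coverage of 98.6% per comparison is what that method implies.
- **That the choice of dose turns on which column is read.** No section ties dose selection to a p-value or an interval. Section 11.2 describes mean plots over time and by dose, repeated-measures analysis and the shape of the dose-response.

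Nor is it a fault that an exploratory dose-finding trial leaves its tests unadjusted. What the reply does not remove is that the protocol never marks the intervals as supplementary, and that its two statements on adjustment conflict for the same contrasts.

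**Conclusion.** The inconsistency is real and lies in current text on the primary comparison. For any dose with an unadjusted p between about 0.014 and 0.10, the protocol's rule says significant while its tabulated interval contains zero; elsewhere the two agree. The intervals are about 1.5 times as wide as ones that match the test.

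These figures depend only on the number of arms, the stated levels and the residual df, and hardly change for df from 165 to 254. The discordance rates (19% to 32% per comparison at n = 52) rest on assumed standardised effects of 0.2 to 0.6, and the widths in points on an assumed SD of 6 to 8.

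The consequence is an ambiguous efficacy table, not an invalid primary analysis or a failed decision rule. It should be corrected, but the trial does not stand or fall on it.

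**What to change.** Use one convention for p-values and intervals, and align the Abstract with section 11.2.

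The protocol states twice that it does not adjust, so the simplest change is to replace the Tukey-Kramer sentence with: unadjusted two-sided 90% confidence intervals for each dose minus placebo, from the same ANCOVA as the tests. Add the same statement to section 11.2, which now specifies no interval for these differences.

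If a multiplicity-adjusted interval is also wanted, label it supportive, use a many-to-one method (Dunnett, four contrasts) and print the matching adjusted p-value beside it. Adjusting both p-values and intervals would also be consistent, but would mean changing the stated policy.

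The cost is wording in the protocol, carried into the SAP; sample size and data collection are unaffected. One small downside should be stated: the primary table then has no simultaneous protection, with a familywise error of about 0.29 for the four comparisons. Settle the choice before unblinding, so that the results cannot influence it.

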It was observed in the pharmacological study on cardiovascular safety in Cynomolgus monkeys that this product could induce elevated blood pressure in the animals, however, no clinically significant change was seen in the blood pressure in the phase I clinical trial on tolerability. In order to ensure subject’s safety, effect of the drug on blood pressure should be noted during the clinical study. In this study, hypertensive patients with poor control of blood pressure should be excluded, and will be monitored through blood pressure in supine and orthostatic blood pressure at each visit.

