### Safety Analysis

The descriptive method will be used for the safety evaluation, and safety variables include adverse event, dose interruption for adverse event, vital signs, laboratory measurement (complete blood cell count, routine urinalysis and serum chemistry), standard 12-lead ECG and physical examination findings.

Type, severity, frequency and the relationship with the investigational product will be tabulated for description for all the adverse events occurred during the study. The subjects that occurred the adverse events leading to withdraw from study and serious adverse events will be particularly noted. Adverse events will be coded using the Medical Dictionary for Regulatory Activities (MedDRA). The shift table will be used for the lab test. Abnormal test items with clinical significance need to be listed.

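### The Abstract plans within-arm paired t-tests on vital signs, which do not test a drug effect; the Safety Analysis section calls the evaluation descriptive and names no test

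*Protocol*

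**What the plan says.** The Statistical analyses row of the Abstract plans three things for vital signs, in consecutive sentences.

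- Description: "Changes in the vital signs from baseline at each visit were described and descriptive statistics were calculated".
- A test inside each arm: "Paired t-test was used to analysis the difference between post-treatment and baseline in the same treatment group".
- A comparison between arms: "The differences of change from baseline between treatments groups were analyzed by using ANCOVA or rank sum test".

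The same row opens with the HAM-D17 analysis, where it sets the level: "statistical tests were conducted using two-sided test and the difference was considered statistically significant (unless otherwise specified) when P value was ≤ 0.10". It adds: "Adjustment was not made when using multiple tests".

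The Safety Analysis part of section 11.2 reads differently: "The descriptive method will be used for the safety evaluation, and safety variables include adverse event, dose interruption for adverse event, vital signs". It names no test for vital signs, either within or between arms.

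The safety question is put in the blood pressure paragraph of section 8.2 (Risks and precautions during the study). After noting raised blood pressure in monkeys, it says: "effect of the drug on blood pressure should be noted during the clinical study".

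**The concern.** In a randomised placebo-controlled trial, the effect of a dose on blood pressure is the change on that dose minus the change on placebo. The paired test has a different null: that the mean post-treatment value equals baseline in that one arm. Anything that moves all arms together makes this null false with no drug effect at all. Examples are recovery, getting used to being measured, or regression to the mean after blood pressure has been screened at entry (exclusion criterion 12).

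A table of five within-arm p-values also invites the reader to compare which doses reached significance. That is not a comparison of doses, because arms that behave identically will often fall on different sides of the threshold. The trial is meant to find a dose and to inform the next phase, so a false contrast in tolerability between neighbouring doses would be unhelpful.

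Separately, someone who follows the Abstract and someone who follows section 11.2 would produce different vital-sign tables.

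**Working it through.** **The texts.** The Abstract prescribes two kinds of test on vital signs. Section 11.2 covers the same variables and prescribes description only. This mismatch needs no arithmetic and no assumption.

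**Size of the within-arm problem.** The protocol gives no figure for these tests, so there is nothing to reproduce.

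Inputs:

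- Five arms of 52 (Abstract, Number of subjects). As a lower case, 200 completers (section 4.6) spread evenly give 200 / 5 = 40 per arm.
- Two-sided level 0.10. Its use for vital signs is an assumption, so 0.05 is shown as well.
- Shared drift d, in SD of the change score, equal in all five arms, with no drug effect. The protocol gives no value, so a range of 0 to 0.5 is assumed.

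Formulas:

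- Rejection in one arm, p: two-sided tail of a noncentral t with n − 1 degrees of freedom and noncentrality d√n.
- Some but not all of the four doses significant: 1 − p⁴ − (1 − p)⁴.

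Example with n = 52 and d = 0.2: the noncentrality is 0.2 × √52 = 1.44 and p = 0.413. The four doses disagree with probability 1 − 0.413⁴ − 0.587⁴ = 1 − 0.029 − 0.119 = 0.852.

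| Drift (SD) | n=52, 0.10: per arm | doses disagree | n=40, 0.10: per arm | doses disagree | n=52, 0.05: per arm | doses disagree |
|---|---|---|---|---|---|---|
| 0 | 0.100 | 0.344 | 0.100 | 0.344 | 0.050 | 0.185 |
| 0.1 | 0.185 | 0.557 | 0.165 | 0.513 | 0.109 | 0.370 |
| 0.2 | 0.413 | 0.852 | 0.346 | 0.803 | 0.293 | 0.743 |
| 0.3 | 0.688 | 0.767 | 0.587 | 0.852 | 0.565 | 0.862 |
| 0.4 | 0.885 | 0.386 | 0.800 | 0.589 | 0.808 | 0.573 |
| 0.5 | 0.972 | 0.107 | 0.928 | 0.258 | 0.943 | 0.211 |

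The zero-drift row is ordinary multiplicity, not the effect of drift. Disagreement peaks at drifts of about 0.2 to 0.3 SD. It falls at 0.5 SD only because almost every arm, placebo included, is then significant.

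**The between-group comparison under the same drift.** In 20,000 simulated trials with no drug effect, each dose was compared with placebo by a two-sample t-test at 0.10, as a simple stand-in for the planned ANCOVA. Each dose was flagged at 0.099 (d = 0.2) and 0.102 (d = 0.3) with n = 52, and at 0.098 and 0.100 with n = 40. The shared drift cancels and the nominal rate holds.

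**The case against.** The strongest reply is that the right analysis is already planned. The sentence straight after the paired test assigns differences between groups to a between-group test, and the simulation shows that shared drift does not disturb it. This stands. A reader might infer from the paired-test sentence that the drug effect on vital signs goes untested, or that an effect offset by drift would be missed. The protocol does not support either reading.

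A reader might also infer that doses will be ranked by which arms reach within-arm significance. No passage says so, and section 11.2 builds the dose-response work on HAM-D17. The harm would come from misreading a table, not from following an instruction.

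Three limits on the figures also stand.

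- The 0.10 level is stated with the HAM-D17 analysis and, in section 11.2, under the primary endpoint. Its use for vital signs is not explicit.
- The drift sizes come from outside the protocol, and a patchwork of significant doses is a probability, not a certainty.
- The false positives at zero drift follow from testing without adjustment, which the protocol openly accepts for an exploratory study.

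Extending the point to body weight would go too far, because the flow chart and section 8.2.1 list weight separately from vital signs.

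Finally, calling safety descriptive does not expressly forbid a test, and the mismatch with section 11.2 touches the between-group sentence as much as the paired one. That is fair, but it does not remove the mismatch: one section names tests for these variables and the other names none.

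**Conclusion.** The point holds in a limited form and its severity is low. The Abstract and section 11.2 prescribe different analyses of vital signs and must be made to agree. The paired t-tests do not address the drug effect raised in section 8.2. They are a misleading addition beside a between-group comparison that does.

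If 0.10 applies, with 52 per arm, no drug effect and a shared drift of 0.1 to 0.3 SD, an arm is flagged about 19% to 69% of the time, and the four doses disagree in about 56% to 85% of trials. At 0.05 and 0.2 SD, the per-arm rate is still about 29%. That the paired test has the wrong null for a drug effect does not depend on the assumed level or drift; only the size does. The study is exploratory, and neither the primary analysis nor the data collection is affected.

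**What to change.** Delete the paired t-test sentence from the Abstract, or replace it with a statement that within-arm changes are descriptive and carry no p-values.

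State one rule in both the Abstract and the Safety Analysis part of section 11.2. Vital signs are summarised descriptively by arm and visit. Any inference rests only on the dose-minus-placebo difference in change from baseline, from ANCOVA with the baseline value as covariate, reported with its confidence interval.

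The cost is a wording change in two places and fewer p-values to report. No new data are needed.
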